#### Secondary Outcomes

Data used to determine the usability as well as the subcategory of feasibility will be assessed through multiple methods (see Table 2). These methods help to get deeper insight and can improve the reliability and validity of the findings [40]. We will combine quantitative (ie questionnaires, task completions, and log events) and qualitative (ie, interviews and field notes) methods to produce a rich data set, which is especially recommended in health informatics research [41,42].

**Table 2 table2:** Secondary outcomes of the usability measures and logged events as well as requested information measures.

Content	Recording method
Field notes (eg, participation in tests and training)	Qualitative and quantitative analysis
Interviews on satisfaction	Qualitative analysis
Number of completed training sessions	Quantitative output of the InCoPE^a^-App
Number of successfully completed testing periods	Quantitative output of the InCoPE-App
Number of rejected exercises	Quantitative output of the InCoPE-App
Kind of rejected exercises	Quantitative output of the InCoPE-App
Mean and range of the actual duration of the tests and the training sessions	Quantitative output of the InCoPE-App
Number and content of telephone calls	Qualitative analysis
Number and content of emails	Qualitative analysis
Satisfaction with the training session	Request after training session
Participation of the participant	Request after training session

^a^InCoPE: Individualized Cognitive and Physical Exercise.

Several forms of field notes, such as participation of participants after each test and exercise session, will be documented during the whole intervention. Additionally, nursing assistants will be asked to submit feedback, and we will regularly get in touch with nursing assistants by phone calls and emails to identify possible problems that arise when delivering the individualized exercise program through the InCoPE app.

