The logged events and other pertinent information (see Table 2) are a substantial part of the usability with their subgenre feasibility. These feasibility measures place focus on app contents instead of human-technology interface. The feasibility measures are used to assess practicality and satisfaction as well as acceptance of the individualized exercise program but also the respective exercises and the testing. To this end, variables aimed at the exercises, testing, and participation will be collected by analyzing logged events during the entire 18-week intervention.

Interviews will focus on satisfaction with the InCoPE-App. The open-ended approach of Georgsson and Staggers [43] will serve as reference to ask users about aspects of the InCoPE-App, ranging from good to poor usability. We will ask 3 questions: (1) What parts of the system did you think were well designed? (2) Which parts of the system did you think were inadequately designed? (3) Do you have any other comments about the system functions and regarding its usability? All interviews will be conducted on a guided basis and will be held in German. With informed consent of the participants, the interviews will be recorded using a voice recorder (Philips DVT2050, Eindhoven, Netherlands).

Additional secondary outcomes will be assessed to obtain a holistic view of the participants who will be trained with the InCoPE-App. These physical and sociodemographic variables and respective assessment tools are presented in Table 3.

**Table 3 table3:** Secondary outcomes on physical and sociodemographic information.

Dimensions	Assessments	Pre	Post	Implemented in the InCoPE^a^-App
Grip strength	Balloon manometer [44]	Yes	Yes	Yes
Frailty	Standardized phenotype of frailty in older adults [45]	Yes	No	Yes
Pain	Single item	Yes	Yes	Yes
Sociodemographic data and medical information	Singe item	Yes	No	No
Body height and weight	Single item	Yes	No	Yes
Fear of falling	FES-I^b^ [46]	Yes	No	No

^a^InCoPE: Individualized Cognitive and Physical Exercise.

^b^FES-I: Falls Efficacy Scale International Version.

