### Sample Size

The sample size for the number of nursing assistants who will evaluate the InCoPE-App with regard to usability was defined using a probabilistic model of problem discovery for formative user research [34]. We defined a sample size comprising 22 participants to have a 90% chance of observing with a probability of 0.1. In the second study phase, outcomes also include usability in addition to the effectiveness of the InCoPE-App with respect to adaptations in physical and cognitive performance in people with dementia. For this reason, each participant will recruit 2 appropriate residents with dementia in accordance with our inclusion and exclusion criteria. We anticipate that our calculated sample size (N=44: intervention group [IG], n=22; control group [CG], n=22) will be appropriate to examine potential trends toward effectiveness of the InCoPE-App.

This sample size allows detection of moderate effects calculated using an ANOVA with repeated measures for within and between interactions. The calculation of the sample size with G*Power version 3.1.9.2 (Heinrich Heine University of Dusseldorf, Germany [47]; effect size ηp² = 0.07, α error probability .05, power 0.95) resulted in 44 participants.

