### Randomization and Concealment

The residents with dementia recruited by nursing assistants will be allocated to either the CG or IG. This allocation will be performed by cluster randomization as it is not possible to blind participants, nursing assistants, or study personnel regarding group allocation. Participants in the CG will only receive conventional treatment such as individualized medication, standard care, or therapeutic applications for 18 weeks. Participants in the IG will receive the individualized exercise program in addition to conventional treatment. To ensure equal conventional treatment for the IG and CG during the intervention, it will be continuously documented.

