### Statistical Methods

All analyses will be performed using SPSS 27.0 (IBM Corp, Armonk, NY). Prior to analysis, plausibility (eg, considering range and distribution) will be checked to minimize errors. The quantitative analysis comprises the evaluation of the usability questionnaires, which will be analyzed with respect to the corresponding guidelines and will be compared with representative data.

The baseline values of physical and cognitive performance will be compared between IG and CG using chi-square tests for categorical data, Mann-Whitney *U* tests for nonparametric variables, and t tests for continuous and normally distributed parameters. Normal distribution will be checked with the Shapiro-Wilk test. Means and standard deviations will be calculated for normally distributed data, and medians and interpercentile ranges will be calculated for non-normally distributed data. A 2-factor ANOVA with repeated measurement will be used to identify treatment effects. In addition, 95% confidence intervals and partial Eta² will be calculated. The log events will be summarized and analyzed descriptively. Potential effects among subgroups based on varying physical or cognitive performance, gender, fear of falling, and logged events (completed training sessions, average duration of the training sessions) will be investigated using chi-square tests and *t* tests.

Qualitative content analysis of the field notes will be conducted [48]. The interviews will be fully transcribed and checked for accuracy. The entire coding process will be independently performed by 2 scientists. The transcripts will be reviewed to identify meaningful content-related aspects. These aspects will be systematically described using a category system. Research questions and interview guidelines will be consulted to deductively derive the main categories. Subcategories will be inductively developed based on the findings (eg, by subsumption). The category system will be tested by 2 scientists who will independently test-code several parts of the qualitative material and subsequently adapt the categories and their definitions. The 2 coding systems will eventually be merged by consensual coding where consensus will be reached.

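### The t and chi-square tests named for subgroup effects cannot show whether the treatment effect varies, and two of the subgroup variables are post-randomisation training logs that only intervention residents have

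*Protocol article*

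**What the plan says.** The Statistical Methods section of the protocol article gives treatment effects their own model: "A 2-factor ANOVA with repeated measurement will be used to identify treatment effects". No subgroup factor is part of it. Subgroups are handled separately: "Potential effects among subgroups based on varying physical or cognitive performance, gender, fear of falling, and logged events (completed training sessions", followed by "average duration of the training sessions) will be investigated using chi-square tests and *t* tests". The sentence just before the subgroup sentence says that log events will be summarised and described.

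Table 2 (Secondary Outcomes) lists "Number of completed training sessions" and the actual duration of training sessions as output of the app. The text below the table says that the variables on exercises, testing and participation are "collected by analyzing logged events during the entire 18-week intervention". Randomization and Concealment states "Participants in the CG will only receive conventional treatment such as individualized medication, standard care, or therapeutic applications for 18 weeks" and, for the other arm, "Participants in the IG will receive the individualized exercise program in addition to conventional treatment". Sample Size gives "N=44: intervention group [IG], n=22; control group [CG], n=22".

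**The concern.** A question about subgroup effects in a randomised trial is normally whether the IG-CG difference is larger in one kind of resident than in another. That is a difference between two differences and needs an interaction term. A t or chi-square test compares two groups, so it answers another question.

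The logged variables raise a second problem. They are measured after allocation and have no values in the control group, so randomisation does not protect any comparison based on them. If fitter residents attend more sessions, a comparison of many with few sessions will partly reflect fitness and could be misread as dose-response.

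What is at stake is the reading of an exploratory result: who benefits, and whether more training helps more. The main test of effectiveness does not depend on it.

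**Working it through.** **1. What the named tests can estimate for a baseline factor.** Take a two-level factor and the change from before to after. There are four cells: CG and IG, each at level 0 and level 1.

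- Level 1 against level 0, pooled over arms: a prognostic difference.
- Level 1 against level 0, within IG: the prognostic difference plus any interaction, not separable.
- IG against CG within each level: two effects, each with its own p value, but no test of their difference.
- Needed: (IG1 − CG1) − (IG0 − CG0). None of the three tests above estimates this contrast.

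**2. Reproducing the planned effect.** Inputs from Sample Size: partial eta squared 0.07, alpha 0.05, power 0.95, N=44, repeated-measures ANOVA with a within-between interaction. There are two measurements (Primary Outcomes). The pre-post correlation is not stated, so 0.5 is assumed.

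- f² = 0.07/0.93 = 0.0753, so f = 0.274.
- λ = f² × N × 2/(1 − ρ) = 0.0753 × 44 × 2/0.5 = 13.25.
- Power with 1 and 42 degrees of freedom is 0.945. The smallest even N reaching 0.95 is 46.

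The stated 44 is thus reproduced to within two residents. At ρ = 0.3 the required N would be 64 and at ρ = 0.7 it would be 28, so 0.5 fits the stated figure best. In units of the SD of change, the planned effect is d = √(4λ/N) = √(4 × 13.25/44) = 1.10.

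**3. Behaviour of the named tests (illustration).** In 20,000 simulated trials, 11 residents per cell, the treatment effect was 1.10 SD in both subgroups, so the true interaction was zero. The prognostic differences are chosen values; the article gives none.

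| Prognostic difference | Pooled t test significant | IG-only t test significant | Interaction test significant | IG-CG significant in one subgroup only |
|---|---|---|---|---|
| 1.10 SD | 90% | 69% | 5% | 43% |
| 0.8 SD | 63% | 43% | 5% | 42% |
| 0 | 2% | 5% | 5% | 43% |

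The pooled and IG-only tests respond to prognosis. Separate tests by subgroup disagree in about 43% of trials even when nothing differs between subgroups. Only the interaction test stays near 5% for the question asked.

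**4. What an interaction can deliver at N=44.** For a subgroup fraction p and 1:1 arms, SE = √(4/(Np) + 4/(N(1 − p))). With p = 0.5 this is √(4/22 + 4/22) = 0.603 SD. The overall effect has SE √(4/44) = 0.302, half as large. The 95% half-width for the interaction is 2.02 × 0.603 = 1.22 SD, wider than the planned effect itself.

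- Interaction equal to the whole planned effect: noncentrality 1.10/0.603 = 1.82 with 40 df, power 43%.
- Interaction half that size: power 14%.
- With a 30/70 split: 37% and 13%.
- Changing ρ alone (equal split, full-size interaction): 32% at ρ = 0.3 and 63% at ρ = 0.7.
- 80% power for the full-size interaction needs about N=108, and 95% about N=176 (ρ = 0.5).

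Clustering by nursing home is left out because no intracluster correlation is given. It would generally lower these figures.

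**5. The logged variables.** CG residents receive conventional treatment only, so they have no app training sessions to count or time. A group-by-sessions interaction therefore cannot be formed. Only an association within the IG is possible, in 22 residents. The Intervention section adds a documented route to confounding: retesting every 3 weeks lets the app adjust duration, intensity and content. Table 1 shows that MMSE, digit span, TUG, 6-meter walk, chair stand and FICSIT-4 are run in the app and are also primary outcomes. To the extent that session duration follows these results, testing outcomes by duration partly tests the app's own adjustment rule.

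**6. Number of tests (illustration).** Table 1 has 7 effectiveness outcomes: QOL-AD, MMSE, digit span, TUG, 6-meter walk, chair stand and FICSIT-4. Counting performance as one or two factors gives 5 or 6 factors. If each is tested once on each outcome, that is 5 × 7 = 35 to 6 × 7 = 42 tests. At 0.05, with all nulls true, 1.75 to 2.1 false positives are expected.

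**The case against.** The fair counter-case is that the article speaks only of potential effects among subgroups, never promises a test of effect modification, and describes the trial as looking for trends. No primary result and no sample size rests on the sentence. The planned ANOVA with confidence intervals remains the test of effectiveness, and description of the logs is already planned. An interaction test at this size would also decide little. All of this stands, and it limits the point to an exploratory analysis. It does not rescue the tests: the article names them, and on no reading do they show whether the treatment effect varies. The planned description of the logs supports the fix, because the next sentence then adds significance tests on two of the same logs.

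Several stronger statements might be inferred but are not supported:

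- That fitter residents do attend more: there are no attendance data, so this is a risk and not a fact.
- That the logs will be split 11 against 11: no cut-point is given.
- That exactly 42 tests are planned: the article does not say which outcomes are crossed with which factors, and performance may be one factor, since the Intervention section uses joint cognitive-motor clusters.
- That subgroup findings will drive roll-out of the app: Dissemination ties this to the overall evaluation of usability and effectiveness.

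The IG size of 22 comes from Sample Size. Primary Outcomes has each assistant deliver the program to 2 residents, which with 22 assistants would make 44 trained residents. Randomization and Concealment is nevertheless explicit that the CG gets conventional treatment only.

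**Conclusion.** The point holds in a limited form. For baseline factors, the named tests do not address whether the IG-CG difference varies. For completed sessions and session duration, they give a non-randomised comparison within one arm, at odds with the descriptive analysis announced one sentence earlier. Both conclusions follow from the text and need no assumption about the data.

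The size of any error cannot be derived from the article. The simulated rates show the mechanism under chosen prognostic differences and are not a forecast for this trial. The power figures assume ρ = 0.5, two equal subgroups, no dropout and no clustering, with the ranges shown. The test count is likewise conditional. The main repeated-measures ANOVA and its result are untouched.

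**What to change.** For physical or cognitive performance, gender and fear of falling, replace the t and chi-square tests with a group-by-time-by-factor interaction, or equivalently a group-by-factor term on change. Report each as an exploratory estimate with a 95% confidence interval, and state which factors and outcomes are examined.

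For completed sessions and average session duration, drop the significance tests. Describe the association with change in the IG only, for example as a plot of change against sessions completed, and state that it is not a treatment effect. This also brings the two sentences on log events into agreement.

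The cost is a change of wording and some analysis work, with no new data or participants. The downside is precision: at N=44 the interaction intervals will be wide, so an interval that includes zero must not be read as evidence that the effect is the same in all residents.

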## Results

Enrollment for the study started in October 2021. We plan to complete the postassessments of the last included nursing home in April 2022. Results are expected to be available in the second half of 2022.

## Discussion

### Summary

Physical activity in addition to conventional treatment can have a beneficial impact on cognitive and physical performance as well as quality of life in people with dementia. Providing scientifically grounded and individualized, multidomain exercise programs is challenging within everyday nursing care. The digital application InCoPE-App enables nursing assistants to regularly test cognitive and physical performance and subsequently train people with dementia based on their individual performance levels. We expect that the individualization of the exercise program as well as regular use ensured by high usability will result in increased physical and cognitive performance as well as quality of life in people with dementia after the 18-week program delivered by the InCoPE app. The increase in cognitive and physical performance may further ease the care demands and needs of people with dementia and thus possibly reduce the workload of nursing assistants.

### Strength and Limitations

Through the innovative and timely development method and thorough evaluation and integration of users’ experiences [49], we expect an application that is highly usable and feasible in everyday care situations. The acceptance of the InCoPE-App will promote its regular usage and thus allow testing and training residents with dementia individually. The regular conduct of physical and cognitive tests that is implemented as an essential part of the app will help to document the progression of disease symptoms and can thus be regarded as an additional objective tool for clinical documentation, which is required on a regular basis in a nursing home setting. The individualization of the exercise program, which has been described as critically important in previous research [9,20], is the key innovative and novel component of the InCoPE-App.

It is unlikely but possible that usability of the InCoPE-App will be rated as low by nursing assistants. In this case, fundamental changes within the application will be required to increase acceptance and practicability, which may have a considerable impact on the effectiveness of the exercise program. There are risks from a technical point of view that might impede the usability of the InCoPE-App, such as possible failure of the tablets to store the data on each tablet. To lower this risk, we will provide the required tablet with the installed InCoPE-App for each participating nursing home. In addition, nursing assistants can contact the research team to report technical issues and get help at any time.

Another limitation is the rather small number of participating people with dementia. This sample size is sufficient to detect moderate within and between interactions. However, it might be too small to statistically detect small effects. The use of the InCoPE-App within everyday life allows us to gain information about everyday feasibility and suitability; thus, results can be more easily transferred to daily routine. 

